## Abstract

**Background:**

Type 1 diabetes (T1D) places an extraordinary burden on individuals and their families, as well as on the healthcare system. Despite recent advances in glucose sensors and insulin pump technology, only a minority of patients meet their glucose targets and face the risk of both acute and long-term complications, some of which are life-threatening.

The JAK-STAT pathway is critical for the immune-mediated pancreatic beta cell destruction in T1D. Our pre-clinical data show that inhibitors of JAK1/JAK2 prevent diabetes and reverse newly diagnosed diabetes in the T1D non-obese diabetic mouse model. The goal of this study is to determine if the JAK1/JAK2 inhibitor baricitinib impairs type 1 diabetes autoimmunity and preserves beta cell function.

**Methods:**

This will be as a multicentre, two-arm, double-blind, placebo-controlled randomized trial in individuals aged 10–30 years with recent-onset T1D. Eighty-three participants will be randomized in a 2:1 ratio within 100 days of diagnosis to receive either baricitinib 4mg/day or placebo for 48 weeks and then monitored for a further 48 weeks after stopping study drug. The primary outcome is the plasma C-peptide 2h area under the curve following ingestion of a mixed meal. Secondary outcomes include HbA1c, insulin dose, continuous glucose profile and adverse events. Mechanistic assessments will characterize general and diabetes-specific immune responses.

**Discussion:**

This study will determine if baricitinib slows the progressive, immune-mediated loss of beta cell function that occurs after clinical presentation of T1D. Preservation of beta cell function would be expected to improve glucose control and prevent diabetes complications, and justify additional trials of baricitinib combined with other therapies and of its use in at-risk populations to prevent T1D.

**Trial registration:**

ANZCTR ACTRN12620000239965. Registered on 26 February 2020. ClinicalTrials.gov NCT04774224. Registered on 01 March 2021

## Administrative information

Note: the numbers in curly brackets in this protocol refer to SPIRIT checklist item numbers. The order of the items has been modified to group similar items (see http://www.equator-network.org/reporting-guidelines/spirit-2013-statement-defining-standard-protocol-items-for-clinical-trials/)

## Introduction

### Background and rationale {6a}

#### Summary

Type 1 diabetes (T1D) places an extraordinary burden on individuals and their families, as well as on the healthcare system. It involves a lifelong need for insulin, along with frequent blood glucose measurements and strict lifestyle regulation. Despite major advances in insulin delivery and continuous glucose monitoring, controlling blood glucose within the normal range is still difficult. T1D is associated with the risk of potentially life-threatening complications, including those which are acute (hypo- or hyperglycaemia and ketoacidosis) and long-term (vascular complications affecting the heart, feet, eyes, kidneys and nerves).

The JAK-STAT pathway is critical for the immune-mediated pancreatic beta cell destruction in T1D. Our pre-clinical data show that inhibitors of JAK1/JAK2 prevent diabetes and reverse newly diagnosed diabetes in the non-obese diabetic (NOD) mouse model of T1D [1, 2]. The goal of this study is to investigate whether the JAK1/JAK2 inhibitor, baricitinib, has activity against the disease process involved in human T1D with the aim of preventing immune-mediated destruction of insulin-producing beta cells.

#### Scientific rationale and aim

In mouse models and humans with T1D, there is evidence that autoreactive T cells destroy the insulin-producing beta-cells in the pancreatic islets [3]. Pro-inflammatory cytokines play an important role in this response to amplify the response and make beta cells more susceptible to immune recognition [4–7].

The JAK-STAT signalling pathway is downstream of type I and II cytokine receptors. When cytokines bind to their receptor, specific receptor-associated Janus kinases (JAKs) are activated by phosphorylation. JAK molecules phosphorylate cytokine receptors, allowing them to selectively bind STAT (signal transducers and activators of transcription) family proteins—proteins that regulate gene expression [8]. A meta-analysis of gene and protein interaction networks amongst 10 different autoimmune diseases showed JAK-STAT and interferon (IFN) signaling as key converging pathways in autoimmune diseases [9]. While STAT1 knockout NOD mice are protected from diabetes [10], blockade or deletion of individual cytokines or their receptors has much less impact on disease [3, 5, 11]. This underscores the rationale for manipulating cytokine signaling pathways rather than specific cytokines.

JAK inhibitors act on T cells and beta cells making them highly attractive candidate therapies for T1D. Furthermore, large clinical trials primarily in rheumatological diseases have shown that baricitinib, and the class of drugs more generally, is effective [12, 13] and well-tolerated [14, 15]. Our lab has successfully employed JAK1/JAK2 inhibitors to reverse established autoimmunity in NOD mice [1, 2]. JAK inhibitor exposure leads to the downregulation of MHC class I on beta cells, reduction in proliferation of islet antigen-specific T cells, reduction in insulitis and prevention of beta-cell loss [2].

The aim of this study is to assess whether the JAK inhibitor baricitinib can slow the progressive, immune-mediated loss of beta cell mass and function that occurs after clinical presentation. This will be measured via plasma C-peptide, a surrogate marker of insulin secretion.

#### Clinical experience with JAK inhibitors

Cytokine inhibition has revolutionized the treatment of autoimmune and inflammatory diseases through monoclonal antibodies that target specific cytokine pathways such as TNF, IL-1, IL-6 and more recently IL-23/IL-12 [16]. JAK inhibitor drugs were introduced through the discovery of tofacitinib, a drug that targets the ATP-binding pocket of JAK3 [17]. Tofacitinib has become a treatment for rheumatoid arthritis and is favourably regarded because it is oral, effective and well tolerated. Baricitinib was designed as a modification of tofacitinib that would inhibit JAK1 and JAK2 rather than JAK3.

Baricitinib has been tested in phase 2 and 3 studies leading up to registration in Europe in 2017 and USA and Australia in 2018. The main indication has been for rheumatoid arthritis with the primary outcome of trials being whether a 20% improvement in a clinical score was achieved (ACR20). These studies include determining the efficacy of baricitinib in patients with inadequate responses to methotrexate [18], comparing baricitinib with methotrexate in patients beginning therapy with disease-modifying agents (RA-BEGIN) [19], the use of baricitinib in patients who were intolerant to DMARDS (RA-Build) [20], baricitinib compared to anti-TNFα therapy (RA-BEAM) [13] and the efficacy of baricitinib in patients with moderate to severe RA with an inadequate response to anti-TNFα therapy (RA-Beacon) [12]. These studies concluded that baricitinib as a single agent is significantly more effective than methotrexate or anti-TNFα treatments and that this effect was seen with 4 mg/d of drug with effects also seen at 2 mg and at higher doses. Approximately 70% of participants achieved ACR20 with baricitinib alone.

Studies with baricitinib have also been carried out for inflammatory bowel disease (both ulcerative colitis and Crohn’s disease), psoriasis and psoriatic arthritis, atopic dermatitis [21], ankylosing spondylitis and systemic lupus erythematosus (SLE) [22, 23]. Tofacitinib has been approved for ulcerative colitis and psoriatic arthritis and a phase 2b dose escalation study of baricitinib showed positive results for psoriasis [24]. Baricitinib has shown efficacy in phase 2 and 3 trials for atopic dermatitis and has recently been approved in Europe for the treatment of moderate to severe disease in adult patients [25]. It has also been used in smaller studies and individual cases in alopecia areata [26], dermatomyositis [27], Candle syndrome and other interferonopathies [28]. More recently, the US Food and Drug Administration has provided Emergency Use Authorization for baricitinib in combination with remdesivir for the treatment of SARS-CoV-2 infections [16]. There continue to be ongoing studies, mostly sponsored by Eli Lilly, for atopic dermatitis in both adults (NCT03559270) and children (NCT03952559), SLE (NCT03843125), juvenile idiopathic arthritis (NCT03773965), giant cell arteritis (NCT03026504), pyoderma gangrenosum (NCT04901325) and hospitalization secondary to SARS-CoV-2 infection (NCT04421027).

### Objectives {7}

The primary objective is to assess whether baricitinib can reduce the loss of plasma C-peptide in patients with new onset T1D after 48 weeks of treatment. The study has several secondary objectives. Firstly, to assess the efficacy of baricitinib at additional timepoints on mitigating the loss of plasma C-peptide; secondly, to assess the effect of baricitinib on secondary clinical outcomes including insulin dose, haemoglobin A1c (HbA1c) and estimated C-peptide (CP_EST_) [29], a surrogate measure of beta cell function; and finally, to assess the safety and tolerability of baricitinib in participants with T1D. Additional exploratory objectives aim to establish the immune mechanism by which baricitinib impacts T1D and evaluate the impact of baricitinib on T1D-associated immune responses.

### Trial design {8}

The study is an investigator-initiated, randomized, two-arm (2:1, baricitinib to placebo), multicentre, double-blind, superiority, phase 2 clinical trial. The participants will be randomly assigned, in a 2:1 ratio, to either baricitinib for 48 weeks or placebo for 48 weeks and therefore will be followed for 96 weeks from the start of treatment.

## Methods: participants, interventions and outcomes

### Study setting {9}

The BANDIT trial is coordinated by the St Vincent’s Institute of Medical Research, Melbourne, Australia. Four tertiary centres in Australia will recruit and manage participants throughout the trial: St Vincent’s Hospital Melbourne, The Royal Melbourne Hospital, The Royal Children’s Hospital Melbourne and the Women’s and Children’s Hospital Adelaide. Data will be collected in Australia.

List of study sites can be accessed via the Australian New Zealand Clinical Trials Registry [ACTRN12620000239965].

### Eligibility criteria {10}

Participants will be deemed eligible by the treating physicians and nurses at the time of T1D presentation and diagnosis at each of the four tertiary hospitals.

#### Inclusion criteria

Participants must meet *all* of the following criteria to be eligible for the study:Male or female aged between 10 and 30 years (inclusive) at screeningDiagnosis of T1D according to ADA criteria within 100 days prior to starting study drugIslet autoantibody positivity (one or more of: GADA, IA-2A, IAA (assessed within one week of commencing insulin therapy), ZnT8A)Stimulated (peak or 90 min) C-peptide >0.2 nM during a 2-h MMTT at the screening visit, or random C-peptide result >0.3 nM during the screening periodParticipants of childbearing age who are sexually active must agree to use of effective birth control until the end of the studyBe able to read, understand and give written informed consentBe willing to comply with intensive diabetes management

#### Exclusion criteria

Participants must *not* meet any of the following criteria:Use of immunosuppressive or immunomodulatory therapies other than inhaled or topical glucocorticoidsCurrent or past history of deep vein thrombosis or pulmonary embolismImpaired renal function defined by estimated glomerular filtration rate (according to the CKD-EPI) of < 60 mL/min/1.73 m^2^LDL cholesterol >4mmol/lElevated liver function tests at screeningAspartate aminotransferase 2x ULNAlanine aminotransferase 2 x ULNClinically significant abnormal laboratory parameters at screening including but not limited to:Haemoglobin < 8 g/LWhite blood cells <2500 cells/μlLymphocyte count <750 cells/μlPlatelets <50,000 cells/μlNeutrophils <1200cells/μLKnown hypersensitivity to baricitinibKnown malignancy with the exception of successfully treated non-metastatic basal cell and squamous cell carcinomaPregnancy, a desire for pregnancy, breast feeding, or a desire to father a child during the studyPatients with current or recent (within 12 weeks of screening) clinically significant comorbidity, including clinically serious viral, bacterial, fungal, or parasitic infection. Viral infections include HBV, HCV, EBV, HIV, recent herpes zoster, and TBTreatment with any investigational product within 30 days or 5 half-lives (whichever is longer) prior to baseline visit, or concurrent participation in a clinical trial with an investigational product or deviceExperienced any of the following within 12 weeks of screening: myocardial infarction, unstable ischemic heart disease, stroke or New York Heart Association Stage IV heart failureAny serious medical condition within 4 weeks of screening which places the participant at an unacceptable risk if he or she were to participate in the study or confounds the ability to interpret data from the study, including, but not limited to, symptomatic cardiovascular, renal, respiratory, hepatic, gastrointestinal, endocrine, haematological and neurological conditions or psychiatric illness/social situations that would limit compliance with study requirementsHave had any major surgery within 8 weeks prior to screening or will require major surgery during the study that, in the opinion of the investigator, would pose an unacceptable risk to the participantHistory of chronic alcohol abuse or IV drug abuse or other illicit drug abuse within 2 years prior to screening

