### Interim analyses {21b}

An interim analysis will be conducted after the week 24 clinical data for the first 21 participants are complete and a report on the study feasibility and safety will be presented to the SRC and the TMG, who oversee all aspects of the trial and perform safety oversight activities.

Safety results will be listed, tabulated using descriptive statistics and plotted when appropriate. Parameters to be studied may include incidence of AEs, vital signs, laboratory parameters, physical examination findings, concomitant medications and other safety analyses as deemed clinically appropriate. For some safety parameters, results may be summarized and plotted separately for adults (participants who were 18 years or older at the time of randomization) and adolescents (participants who were at least 10 but not yet 18 at randomization). Analyses of AEs may include special categories of AEs, such as rashes, infections and autoimmune disorders. AEs may also be summarized by time of onset.

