## Abbreviations

ADA: American Diabetes Association
AE: Adverse event
ALT: Alanine aminotransferase
ANOVA: Analysis of variance
AST: Aspartate aminotransferase
AUC: Area under the curve
CMV: Cytomegalovirus
CRF/eCRF: Case report form/electronic case report form
CGM: Continuous glucose monitoring
CKD-EPI: Chronic Kidney Disease Epidemiology Collaboration
CyTOF: Mass cytometry
DC: Dendritic cell
DCCT: Diabetes Control and Complications Trial
DKA: Diabetic ketoacidosis
DMSO: Dimethylsulfoxide
DVT: Deep vein thrombosis
EBV: Epstein-Barr virus
FCS: Foetal calf serum
GADA: Glutamic acid decarboxylase antibodies
GCP: Good Clinical Practice
GI: Gastrointestinal
HbA1c: Haemoglobin A1c
HDL: High-density lipoprotein
HepB/HBV: Hepatitis B/hepatitis B virus
HepC/HCV: Hepatitis C/hepatitis C virus
HIV: Human immunodeficiency virus
HLA: Human leukocyte antigen
HREC: Human Research Ethics Committee
IAA: Insulin autoantibodies
IA-2A: Insulinoma-associated-2 autoantibodies
ICH: International Conference on Harmonisation
IFN: Interferon
ITT: Intention to treat
JAK: Janus kinase
LDL: Low-density lipoprotein
LFT: Liver function test
MMTT: Mixed-meal tolerance test
NHMRC: National Health and Medical Research Council
NK cell: Natural killer cell
NOD: Nonobese diabetic
PBMC: Peripheral blood mononuclear cell
PI/CPI: Principal Investigator/Coordinating or Chief Principal Investigator
PICF: Patient information consent form
PLN: Pancreatic lymph node
RA: Rheumatoid arthritis
RGO: Research Governance Organization
SAE: Serious adverse event
SAP: Statistical analysis plan
SoA: Schedule of assessments
SRC: Safety Review Committee
STAT: Signal transducers and activators of transcription
SVI: St Vincent’s Institute
TB: Tuberculosis
T1D: Type 1 diabetes
TMG: Trial Management Group
ULN: Upper limit of normal
VZV: Varicella zoster virus
ZnT8: Zinc transporter 8

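### One CKD-EPI cut-off sets renal eligibility from age 10; under standard formulas it reads above a height-based estimate in minors, so some below 60 would clear the numeric exclusion

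*Protocol article*

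**What the plan says.** Under Exclusion criteria, the protocol article defines impaired renal function by "estimated glomerular filtration rate (according to the CKD-EPI) of < 60 mL/min/1.73 m^2". This is the only numeric renal criterion, and it is not varied by age. The Abbreviations list only expands the name ("CKD-EPI: Chronic Kidney Disease Epidemiology Collaboration"). No equation version, paediatric variant or formula is given.

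Under Inclusion criteria, participants may be 10 to 30 years old at screening. Minors are a planned part of the trial. Study setting {9} includes "The Royal Children’s Hospital Melbourne and the Women’s and Children’s Hospital Adelaide" among the four sites, and Interim analyses {21b} allows some safety results to be summarised separately for "adolescents (participants who were at least 10 but not yet 18 at randomization".

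Other exclusion clauses could also catch renal disease. One covers clinically significant abnormal laboratory values and is open-ended. One covers recent clinically significant comorbidity. A third covers serious conditions in the 4 weeks before screening, including "symptomatic cardiovascular, renal, respiratory, hepatic, gastrointestinal, endocrine, haematological and neurological conditions". None of them sets a GFR limit.

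**The concern.** In its standard creatinine forms, CKD-EPI takes creatinine, age and sex. It has no term for body size. A child with little muscle produces little creatinine, and an equation without height or another size term reads that low creatinine as high filtration. A single CKD-EPI limit would then not mean the same thing at age 10 as at age 30.

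At stake is a safety criterion. It decides which participants with reduced renal function are kept from study drug, and it would be most lenient in the youngest. The primary endpoint, the power and the planned analyses are not affected.

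**Working it through.** The document gives no eGFR figure to reproduce, so the check asks how the written limit behaves across the ages admitted.

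**Inputs from the document:** limit 60 mL/min/1.73 m², CKD-EPI named, lower age 10.

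**Assumed inputs** (S = serum creatinine in mg/dL):
- CKD-EPI 2009, for S above k: 141 × (S/k)^−1.209 × 0.993^age, times 1.018 if female; k = 0.7 female, 0.9 male.
- CKD-EPI 2021, for S above k: 142 × (S/k)^−1.200 × 0.9938^age, times 1.012 if female; same k.
- Height-based comparator (bedside Schwartz): 0.413 × height in cm / S.
- Heights (girl/boy, cm): 138/138 at age 10, 151/149 at 12, 160/164 at 14, 162/173 at 16, 163/175 at 17.

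**Step 1: what CKD-EPI reads when the height-based estimate is exactly 60.** At age 10 and 138 cm, S = 0.413 × 138 / 60 = 0.95.
- Boy, 2009: 141 × (0.95/0.9)^−1.209 × 0.993^10 = 141 × 0.937 × 0.932 = 123.
- Girl, 2009: 141 × (0.95/0.7)^−1.209 × 0.993^10 × 1.018 = 141 × 0.691 × 0.932 × 1.018 = about 93.

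**Step 2: the height-based value at which CKD-EPI first falls to 60.** For the boy of 10 (2009), solve (S/0.9)^1.209 = 141 × 0.932 / 60 = 2.19. This gives S = 1.72, and 0.413 × 138 / 1.72 = 33. For the girl of 10, S = 1.36 and the value is 42.

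All cells, 2009/2021:

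| Age | Sex | CKD-EPI at height-based 60 | Height-based value at CKD-EPI 60 |
|---|---|---|---|
| 10 | girl | 93/94 | 42/41 |
| 10 | boy | 123/125 | 33/33 |
| 12 | girl | 82/83 | 46/46 |
| 12 | boy | 111/113 | 36/35 |
| 14 | girl | 75/76 | 50/49 |
| 14 | boy | 97/99 | 40/39 |
| 16 | girl | 73/74 | 51/50 |
| 16 | boy | 90/92 | 43/42 |
| 17 | girl | 72/73 | 52/51 |
| 17 | boy | 88/90 | 44/43 |

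**Step 3: one case.** A boy of 10 and 138 cm with a height-based estimate of 45 has S = 0.413 × 138 / 45 = 1.27. CKD-EPI 2009 then gives 141 × (1.27/0.9)^−1.209 × 0.932 = 87, so he clears the numeric exclusion. A girl of 17 and 163 cm with the same estimate has S = 1.50 and CKD-EPI of about 51, so she is excluded.

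**Step 4: sensitivity to height.** Heights from 125 to 185 cm were tried at ages 10, 14 and 17, for both sexes and both versions. At a height-based 60, CKD-EPI ran from 62 (girl of 17, 185 cm, 2009) to 135 (boy of 10, 125 cm, 2021). It was above 60 in every cell. The size of the gap depends on height, but its direction does not.

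**The case against.** The strongest objection is that the document prints no equation, names no CKD-EPI version and gives no heights, so its age range and renal rule conflict only through formulas brought in from outside. This stands as a limit on the figures, and they are labelled as assumptions for that reason. It does not remove the point: the article itself names CKD-EPI and applies it to everyone from age 10, and the direction held under both versions and all heights tried.

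Three stronger readings are tempting, and the documents do not support them.
- *A reader might infer that minors with a true GFR well below 60 are declared eligible.* The comparator is itself a creatinine-based estimate, not measured GFR. Clearing one exclusion also does not make anyone eligible. The open-ended laboratory clause needs no symptoms and lets an investigator exclude on a clinically significant creatinine, and the comorbidity clauses add to it. Because none carries a GFR limit, they are only a partial backstop.
- *A reader might infer that CKD-EPI reads far too high in all adolescents.* The gap is large in the youngest, above all in boys. In a girl of 17 it is 12–13 units.
- *A reader might infer that minors with impaired function have been enrolled.* Nothing in the document shows this, and few people with recent-onset type 1 diabetes are likely to lie in the affected band.

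It can also be said that the article condenses a fuller protocol (Version 6), which may hold an age-specific instruction. If so, the sponsor need only confirm it. As published, the rule is stated for all ages, so this is not a matter of missing detail. Finally, Trial status reports about 80 of the planned 83 already randomised, so little screening remains. That changes which part of the fix is useful, not whether the rule is right.

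**Conclusion.** The point holds in a limited form. Under the assumed equations and heights, the written limit of 60 acts in minors like a height-based value of about 33–42 at age 10 and 43–52 at age 17. A minor between that value and 60 clears the numeric renal exclusion. At a height-based 60, the excess of CKD-EPI runs from 12–13 units (girl of 17) to 63–65 units (boy of 10).

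Marked impairment, below roughly 33–52 depending on age and sex, is still excluded. Adults aged 18–30 are outside this argument. The number affected is probably small and cannot be estimated from the document. The equation and the age range should be reconciled, because the criterion is a safety rule and correcting it is cheap.

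**What to change.** Reconcile the renal item under Exclusion criteria with the age range under Inclusion criteria. Keep the sponsor's threshold and keep CKD-EPI for adults. For participants under 18, name an eGFR equation valid at that age (height-based), and state the version of each equation used.

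With recruitment nearly complete, the more useful step is to recalculate screening eGFR for minors already randomised and refer any value below the stated limit to the Safety Review Committee. What follows for such a participant is for the committee and investigators to decide.

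The cost is a wording change and an eCRF formula. Height must be recorded, which fits the full examination already scheduled at screening; for enrolled minors it has to be retrieved from the record. The downside is that a very few minors may be reclassified.
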